### Data Collection Methods

Data collection will involve collecting information pertaining to demographics, delayed dental healing, bisphosphonate history and medical history. Data collection forms and telephone interviews for controls will be the same as that used for cases.

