#### Telephone interview

A telephone interview will be conducted with all consenting participants in order to confirm inclusion/exclusion criteria (most of which may already be evident from the patient's dental file) and to determine socio-economic status, dental health information and a medical history check including bisphosphonate history, medication profile and smoking history. The telephone interview will last approximately 10 minutes. The telephone questionnaire will be modelled on the Adult Oral Health Survey [38] and include questions relating to dental health and general information such as socio-economic status and educational status. A medication check list will also be completed with each case regardless of the data collected in the original data collection form in order to cross match bisphosphonate history, other medical history which could contribute to impaired wound healing and smoking history.

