#### Power and sample size

The sample size estimate is based upon the assumption that the overall prevalence of bisphosphonate use in post-menopausal women is around 10%. Based on Australian Pharmaceutical Benefits Scheme (PBS) and Australian Bureau of Statistics (ABS) data the upper limit estimate is 19% [39]. Assuming that approximately 50% of these patients have used bisphosphonate for at least one year, then 10% prevalence of long-term use in this population appears to be a reasonable estimate. It is hypothesised that the prevalence of bisphosphonate use among those with delayed dental healing may be greater than 10%. A recent case series of patients with frank jaw necrosis found that all were treated with bisphosphonates [19]. We infer from this that the true proportion of women with DDH taking bisphosphonates may be greater than 30% - 50%. Given the expected low prevalence of DDH, the study plans to recruit 'controls' and 'cases' in a ratio of 4:1. An observed prevalence of greater than or equal to 30% bisphosphonate use amongst women with DDH would correspond to an odds ratio of around 3.85. Hence, for the purpose of this study, the minimum detectable difference will correspond to an OR greater than or equal to 3.85. This value is based upon a conservative estimate of the effect expected, rather than what is considered clinically important. The most relevant measure of clinical importance will be one derived from a cohort study, that is where the effect of bisphosphonate use can be represented in terms of a relative and/or absolute risk of delayed dental healing. Whilst ideal, this would require a very large sample and long-term follow-up.

A total sample of around 269 subjects (54 cases and 215 controls) will provide 90% power to detect a true OR of at least 3.85, given the expected prevalence of 10% bisphosphonate use amongst post-menopausal women in the community.

The relationship between bisphosphonate use and delayed dental healing will be assessed using a multivariate logistic model incorporating age, duration of exposure, relevant co morbidities, concurrent treatment, and other potential confounders as covariates.

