The present study also relies on recruitment of specialists to allow access to patient records followed by recruitment of cases and controls. All oral and maxillofacial specialists and special needs dentists in the state of Victoria will be invited to participate in the study but it will be difficult to control for ascertainment bias. Are practitioners who see delayed dental healing and ONJ more willing to allow review of their patient records? Are those who have a greater interest in the role played by bisphosphonates more likely to want to become involved? It is difficult to control for this even with the use of random sampling because practitioners' consent is required to allow file review. To some degree the same can also be said for patients with delayed dental healing. The patient information and consent brochure stipulates that this is an important study to further our understanding of the link between delayed dental healing and bisphosphonate use. Whether an individual who has taken a bisphosphonate may be more or less likely to participate is difficult to determine. Another potential limitation of the study is recollection bias given that some data will be collected via participant telephone interview. Furthermore, control subjects reading the patient information and consent brochure may feel that the study does not really benefit them and hence may be less likely to respond. The same can also be said for the general dental practitioners via whom the control subjects will be identified. If they have little experience with patients taking bisphosphonates or delayed dental healing, then they may have little motivation to allow a third party to access their patient records.

A key feature of the present study relates to the definition of DDH and ONJ. In 2005 the definition of osteonecrosis of the jaw was unclear and constantly changing in the literature and as such it was difficult to adhere to a single definition. The main disparity at the time was related to the length of time a wound took to heal before it fell into the category of osteonecrosis of the jaw. Initial healing, that is re-epithelialisation, of dental wounds such as those from dental extractions usually takes between 1 and 2 weeks [43]. Once the clot forms, fibrin and connective tissue begins to develop before the wound (in this case a dental socket) is closed over by epithelium. It then takes some weeks for the underlying socket to fill with bone and healing to be complete.

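### Two sections disagree on whether controls get the medication check list that cross-matches bisphosphonate history; read literally, it is for cases only and could push the odds ratio upward

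*Protocol article*

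**What the plan says.** All references are to the protocol article.

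- **Data Collection Methods**, opening paragraph: "Data collection forms and telephone interviews for controls will be the same as that used for cases".
- **Telephone interview**, who is called: "A telephone interview will be conducted with all consenting participants in order to confirm inclusion/exclusion criteria". For everyone, the call includes "a medical history check including bisphosphonate history, medication profile and smoking history".
- **Telephone interview**, last sentence: "A medication check list will also be completed with each case regardless of the data collected in the original data collection form". The purpose given is "in order to cross match bisphosphonate history, other medical history which could contribute to impaired wound healing and smoking history".
- **Discussion**: "Another potential limitation of the study is recollection bias given that some data will be collected via participant telephone interview".

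Potential covariates names bisphosphonate use as the exposure of interest. Power and sample size plans a logistic model with adjustment for comorbidities, concurrent treatment and other confounders.

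**The concern.** A case-control comparison needs exposure to be ascertained in the same way in both groups. Within one paragraph, the Telephone interview section uses one term for everybody who is called and another for those who complete the check list, and it presents the check list as an addition to the interview. Elsewhere, when the article uses 'case' for a person, it means someone with adjudicated delayed healing, as opposed to a control: Case Recruitment speaks of verified cases, and Recruitment of Control Subjects matches four controls to each case. On that usage, the check list is an extra step for one group.

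If it were run that way, past or present bisphosphonate use missing from the dental file would be recovered more often in cases than in controls. That is differential misclassification of the tested exposure, and it can produce an association where none exists. The check list also covers smoking and other medical history, so the adjustment covariates would be measured unequally too. The planned logistic model cannot correct for this.

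**Working it through.** **Step 1. The rules side by side.**

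| Element | Cases | Controls |
|---|---|---|
| Data collection form | yes | yes, the same (Data Collection Methods) |
| Telephone interview with bisphosphonate history and medication profile | yes | yes (Telephone interview; Data Collection Methods) |
| Medication check list to cross-match the file | yes (Telephone interview) | yes if the check list counts as part of the interview; no if the sentence is read literally |

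Only the last cell is unsettled. The equal-procedure sentence names forms and interviews but not the check list. The check list sentence stands under the interview heading but names cases.

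**Step 2. The plan's own figures.** Power and sample size gives 10% use in the source population ("10% prevalence of long-term use in this population appears to be a reasonable estimate") and 30% in cases ("An observed prevalence of greater than or equal to 30% bisphosphonate use amongst women with DDH would correspond to an odds ratio of around 3.85").

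OR = (0.30/0.70) / (0.10/0.90) = 0.4286/0.1111 = 3.86, which agrees with the stated 3.85. The stated 54 cases and 215 controls are also reproduced: 54 and 216 at 90% power and 1:4, with a continuity correction and an assumed two-sided 5% level. The 10% and 30% are therefore the right inputs for an illustration.

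**Step 3. Effect of unequal sensitivity.** Let p1 and p0 be true use in cases and controls, and s1 and s0 the probability that true use is recorded. With no false positives:

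observed OR = [p1·s1/(1 − p1·s1)] / [p0·s0/(1 − p0·s0)]

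The article gives no sensitivities. The values below are assumptions, with s1 = 0.95.

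*No true effect, p1 = p0 = 0.10.* Case odds: 0.095/0.905 = 0.10497.

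- s0 = 0.95: 0.10497/0.10497 = 1.00
- s0 = 0.90: control odds 0.09/0.91 = 0.09890; OR = 1.06
- s0 = 0.80: control odds 0.08/0.92 = 0.08696; OR = 1.21

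*Design effect, p1 = 0.30, p0 = 0.10 (true OR 3.86).* Case odds: 0.285/0.715 = 0.39860.

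- s0 = 0.95: 0.39860/0.10497 = 3.80
- s0 = 0.90: 0.39860/0.09890 = 4.03
- s0 = 0.80: 0.39860/0.08696 = 4.58

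Equal sensitivity leaves a null odds ratio at exactly 1.00 and moves the design odds ratio slightly toward 1. Inflation appears only when the two groups differ.

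**The case against.** The strongest reply is that the article already answers the question. The check list sentence does not exclude controls. It sits under the interview heading, and the opening of Data Collection Methods extends the interview to controls unchanged. On that reading both groups get the check list, and the wording is merely loose. The article is also condensed, and the interview script is not shown. This is a plausible reading and it stands as one. It does not remove the inconsistency: the equal-procedure sentence does not mention the check list, and staff working from the Telephone interview section alone would complete it for cases.

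A reader might go further and infer any of three things that the documents do not support.

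- *That controls have no systematic check of exposure.* Every consenting control is asked about bisphosphonate history and medication profile by telephone. The possible gap is one extra prompted step, not verification against none.
- *That control records are known to be poorer.* The Discussion's remark about community dentists with little experience of bisphosphonates is conditional. It concerns their willingness to give access to records, not how well those records document the drug.
- *That the odds ratio will be inflated, perhaps greatly.* Any such figure depends on assumed sensitivities. Because both groups are asked directly about the exposure, the smaller gaps are the more plausible ones.

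The recollection bias admitted in the Discussion is a separate matter. It applies even when both groups get identical instruments, so the admission neither supports this point nor disposes of it.

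**Conclusion.** The article is inconsistent on how the tested exposure is verified in controls, and this should be corrected. It does not show that exposure will be measured unequally, so upward bias is a possibility that depends on the literal reading of one sentence.

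The size cannot be determined from the document. Under the assumptions shown (perfect specificity, 95% sensitivity in cases, 90% or 80% in controls), a true odds ratio of 1 would be observed as 1.06 or 1.21, and the design value of 3.86 as 4.03 or 4.58. The upward direction rests on the check list mainly recovering missed use. If it mainly removed wrongly recorded use, the direction could differ. The point is a low-cost clarification of a validity condition and not a fatal flaw in the design.

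**What to change.** In the Telephone interview section, change 'each case' to 'each case and each control'. State that the check list uses the same prompts in both groups, and that one common rule decides which source prevails when file and interview disagree. In the results, report agreement between file and check list separately for cases and controls, so that a reader can see whether ascertainment was comparable.

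The cost is a small change of wording and a few minutes added to a call of about 10 minutes that controls already receive. The sample size of 54 cases and 215 controls does not change.

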### Ethics Approval

Human Research and Ethics Committee approvals have been obtained from: Melbourne Health (2005.242) (hospital and private practice cases and controls), Austin Heath (H2006/02599; H2010/03794), The Alfred (17/09), Barwon Heath (10/99), Dental Health Services Victoria (197), Southern Health (09069A), St Vincent's Hospital (009/09) and Western Health (2005.242).

### Statistical Analysis

Demographic and clinical characteristics of cases and controls will be presented to assess whether these variables are associated with delayed dental healing.

#### Power and sample size

The sample size estimate is based upon the assumption that the overall prevalence of bisphosphonate use in post-menopausal women is around 10%. Based on Australian Pharmaceutical Benefits Scheme (PBS) and Australian Bureau of Statistics (ABS) data the upper limit estimate is 19% [39]. Assuming that approximately 50% of these patients have used bisphosphonate for at least one year, then 10% prevalence of long-term use in this population appears to be a reasonable estimate. It is hypothesised that the prevalence of bisphosphonate use among those with delayed dental healing may be greater than 10%. A recent case series of patients with frank jaw necrosis found that all were treated with bisphosphonates [19]. We infer from this that the true proportion of women with DDH taking bisphosphonates may be greater than 30% - 50%. Given the expected low prevalence of DDH, the study plans to recruit 'controls' and 'cases' in a ratio of 4:1. An observed prevalence of greater than or equal to 30% bisphosphonate use amongst women with DDH would correspond to an odds ratio of around 3.85. Hence, for the purpose of this study, the minimum detectable difference will correspond to an OR greater than or equal to 3.85. This value is based upon a conservative estimate of the effect expected, rather than what is considered clinically important. The most relevant measure of clinical importance will be one derived from a cohort study, that is where the effect of bisphosphonate use can be represented in terms of a relative and/or absolute risk of delayed dental healing. Whilst ideal, this would require a very large sample and long-term follow-up.

A total sample of around 269 subjects (54 cases and 215 controls) will provide 90% power to detect a true OR of at least 3.85, given the expected prevalence of 10% bisphosphonate use amongst post-menopausal women in the community.

The relationship between bisphosphonate use and delayed dental healing will be assessed using a multivariate logistic model incorporating age, duration of exposure, relevant co morbidities, concurrent treatment, and other potential confounders as covariates.

The prevalence of DDH in the target population will be estimated using data collected to determine case numbers in both bisphosphonate-treated and non-bisphosphonate-treated patients. We will also record cases of DDH occurring in non-bisphosphonate-treated patients with a diagnosis of benign bone disease where bisphosphonates may be indicated (i.e. osteoporosis, Paget's disease of the bone).

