## Hypothesis

The hypothesis to be tested is that long-term (more than 1 year's duration) bisphosphonate use for the treatment of post-menopausal osteoporosis or other benign bone disease is associated with impaired dental healing.

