### Recruitment of Control Subjects

Each case will be matched with four controls randomly selected from those who have undergone dental treatment at the same dental practice from which the case originated. If access cannot be obtained to records from the originating dental practice, then a similar type of practice e.g. private practice or hospital - based practice, within a 10 km radius will be approached to provide control subjects. They will be matched for age (>50 years), gender and visit window period and will have no known defect in dental wound healing. If controls cannot be matched to the 6-month visit window period then they will be matched to within 12 months of the visit window period. Controls will be contacted by mail as for cases to obtain informed consent to study participation.

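### The 10% exposure prevalence behind the 90% power is labelled both overall and long-term use; as long-term use it follows only from the 19% upper limit, and at 5% power for an OR of 3.85 is about 71% to 78%

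*Protocol article*

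**What the plan says.** All the inputs stand in one paragraph, under Power and sample size in the protocol article.

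- The starting assumption is that "the overall prevalence of bisphosphonate use in post-menopausal women is around 10" per cent.
- From national prescribing and population data, "the upper limit estimate is 19" per cent.
- The next step assumes that "approximately 50% of these patients have used bisphosphonate for at least one year", and concludes: "then 10% prevalence of long-term use in this population appears to be a reasonable estimate".
- Exposure in cases is put at 30% or more, which against 10% gives the OR of about 3.85. No duration of use is attached to the 30%.
- The planned sample is 215 controls with 54 cases, and the power statement made for it reads: "will provide 90% power to detect a true OR of at least 3.85, given the expected prevalence of 10% bisphosphonate use". It does not say whether this is any use or long-term use.

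The Hypothesis section defines the exposure as "long-term (more than 1 year's duration) bisphosphonate use". The criteria under Case Recruitment set a minimum age of 50 and no sex restriction. Under Recruitment of Control Subjects the rule is: "They will be matched for age (>50 years), gender and visit window period".

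**The concern.** The paragraph gives one number two meanings. If only about half of users have used the drug for a year or more, overall use and long-term use cannot both be 10%. The hypothesis concerns long-term use, so the long-term figure should drive the power. The text reaches 10% for it only by halving a value that it calls an upper limit, and the power sentence then calls the result expected.

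This matters because, at a fixed OR, power falls as exposure in controls becomes rarer. If long-term use among controls is nearer 5%, the study does not have 90% power at 3.85, and a null result would say less about an OR of that size than the stated power suggests.

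The population is a second, smaller gap. The prevalence inputs describe post-menopausal women, but men aged 50 or over can enter as cases and then bring in male controls through gender matching.

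**Working it through.** **Inputs from the article:** 54 cases, 215 controls, ratio 4:1, OR 3.85, power 90%, control exposure 10%, overall use 10%, upper limit 19%, long-term share about 50%.

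**Assumed:** two-sided alpha of 0.05, which the article does not state, and an unmatched, unadjusted comparison of two proportions.

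**1. The effect size.** (0.30/0.70)/(0.10/0.90) = 3.857, matching the stated 3.85. Conversely, OR 3.85 at 10% gives case exposure of 0.385/(0.90 + 0.385) = 29.96%.

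**2. The sample size.** With r = 4, d = p1 − p0 and p̄ = (p1 + 4·p0)/5:

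n = [1.96·√(5·p̄(1−p̄)) + 1.2816·√(4·p1(1−p1) + p0(1−p0))]² / (4d²)

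For p1 = 0.30 and p0 = 0.10, p̄ = 0.14 and n = 47.5. The continuity-corrected size, (n/4)·[1 + √(1 + 10/(4nd))]², is 53.6, that is 54 cases. A one-sided test gives 46 corrected and 40 uncorrected, so the two-sided, corrected version is the one that reproduces the plan.

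**3. The prevalence chain.** 0.5 × 19% = 9.5%, rounded to 10%. 0.5 × 10% = 5%.

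**4. Power with 54/215 and the OR held at 3.85.**

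Power = Φ[(d − c − 1.96·se0)/se1], where c = 0.5(1/54 + 1/215) = 0.0116 (zero if uncorrected), se0 uses the pooled proportion and se1 the two separate proportions.

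At 5%:
- Case exposure is 0.1925/1.1425 = 16.85%, so d = 0.1185.
- The pooled proportion is (54 × 0.1685 + 215 × 0.05)/269 = 0.0738, so se0 = 0.0398; se1 = 0.0531.
- Corrected: (0.1185 − 0.0116 − 0.0780)/0.0531 = 0.54, power 70.7%.
- Uncorrected: (0.1185 − 0.0780)/0.0531 = 0.76, power 77.7%.

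The same formula over the range:

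| Use in controls | Power, corrected | Power, uncorrected | OR detectable with 90% power, corrected |
|---|---|---|---|
| 5% | 70.7% | 77.7% | 5.3 |
| 7% | 81.5% | 86.2% | 4.5 |
| 9.5% | 89.1% | 92.1% | 3.9 |
| 10% | 90.1% | 92.8% | 3.84 |

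Exact binomial enumeration at 5% gives 71.4% (Yates), 73.8% (Fisher) and 79.2% (uncorrected chi-square). Keeping 90% power for OR 3.85 at 5% would take 93 cases at 4:1 (corrected).

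**5. Holding the case exposure instead.** With 30% in cases against 5% in controls, the OR is (0.30/0.70)/(0.05/0.95) = 8.14 and power is about 99%.

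**6. Men.** The article gives neither the share of men nor their use, so only an assumed range is possible. With women at 10%, corrected power at OR 3.85 runs from 74% (50% men with 1% use: 0.5 × 10% + 0.5 × 1% = 5.5%) to 89% (10% men with 5% use: 0.9 × 10% + 0.1 × 5% = 9.5%).

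**The case against.** The strongest reply is that the opening 10% is loose wording for the figure derived two sentences later: 19% halved is 9.5%, called 10%. On that reading, halving 10% again applies the factor twice. This is a fair reading. A reader might infer that 5% is the plan's own central prevalence, and the document does not support that: it never states 5%. What remains is that the word overall would then be wrong, and that 10% would still rest on an upper limit while being called expected.

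Second, the loss of power depends on holding the OR. With 30% in cases held, power rises, as step 5 shows. That is correct, but the plan's claim is 90% power for a true OR of at least 3.85, so the OR is the quantity to hold when testing that claim.

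Third, the power sentence already makes its claim conditional on 10%. It does, but without saying which exposure is meant or that the 10% comes from an upper limit. If any use were meant, the 19% limit would apply and power would be about 98%. That exposure would not be the one in the hypothesis.

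Two further inferences are tempting and should not be drawn. One is that the 30% in cases refers to use of any length, so that the two sides of the OR are known to differ. The article gives no duration there, so the exposure is undefined and a mismatch is not shown. The other is that describing the estimate as conservative is wrong. The word applies to the effect assumption, where 30% is the low end of the 30% to 50% mentioned, and says nothing about control prevalence.

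**Conclusion.** The point holds as a fault in an input and its labelling; the sample-size calculation is correct for the inputs used. For the exposure in the hypothesis, 90% power at OR 3.85 is reached only at the upper end of what the article's own figures support. If overall use is 10%, as the paragraph opens, power for that OR is about 71% to 78% and the risk of missing it rises from about 10% to between 22% and 29%.

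These figures assume two-sided 0.05, an unmatched and unadjusted comparison, and a fixed OR of 3.85. The effect of including men has an unknown size, because the article gives no prevalence for them.

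**What to change.** Keep 54 cases and 215 controls, and revise the sample-size paragraph as follows:

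1. Use one exposure definition, more than one year of use as in the hypothesis, for the prevalence in both cases and controls.
2. Correct the overall and long-term labels, and say that 10% long-term use is half of the 19% upper limit.
3. Give power and detectable OR for control prevalences from 5% to 10%, and tie 90% at OR 3.85 to the 10% upper-end value.
4. State that the prevalences are for post-menopausal women while men are eligible. Show any lower values that allow for men as assumptions, with a range.
5. State alpha and sidedness, since the figures depend on them. The word conservative may stay if it is limited to the 30% effect assumption.

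The cost is rewording and a less favourable power statement. No extra participants are needed, and design and analysis are unchanged.

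### The 10% control prevalence behind the 90% power is half of a stated upper limit but is presented as the expected value; read literally, the section's overall figure gives 5%

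*Protocol article*

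**What the plan says.** All the figures stand in the protocol article, under Power and sample size, in this order.

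- The sample size is said to rest on the assumption that "the overall prevalence of bisphosphonate use in post-menopausal women is around 10"%.
- From national prescription and population data, "the upper limit estimate is 19"%.
- A duration restriction follows: "Assuming that approximately 50% of these patients have used bisphosphonate for at least one year".
- The conclusion is: "then 10% prevalence of long-term use in this population appears to be a reasonable estimate".
- On the effect: "An observed prevalence of greater than or equal to 30% bisphosphonate use amongst women with DDH would correspond to an odds ratio of around 3.85", and "the minimum detectable difference will correspond to an OR greater than or equal to 3.85".
- The power statement gives 54 cases and 215 controls 90% power for a true OR of at least 3.85, "given the expected prevalence of 10% bisphosphonate use amongst post-menopausal women in the community".

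The Hypothesis section sets the exposure: "long-term (more than 1 year's duration) bisphosphonate use for the treatment of post-menopausal osteoporosis or other benign bone disease is associated with impaired dental healing". Long-term prevalence is therefore the relevant control input. The power sentence itself names no duration.

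**The concern.** If about half of users are long-term, overall use and long-term use cannot both be 10%. The printed derivation yields 10% long-term use only when the 50% is applied to the figure that the section calls an upper limit. The power sentence then treats the result as expected.

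The consequence runs one way. At a fixed OR, fewer exposed controls mean less power. The section calls its choice of effect size conservative, but its prevalence input is not. If long-term use among controls is lower than 10%, the study could miss an OR of 3.85 more often than the advertised one time in ten, and a null result on a safety question could be read as more reassuring than it is.

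**Working it through.** **Inputs.** From Power and sample size: overall use 10%, upper limit 19%, long-term share 50%, case exposure 30%, OR 3.85, 54 cases, 215 controls, power 90%. Alpha and sidedness are not stated. I assume two-sided 5%; with a continuity correction this reproduces the stated size.

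**Step 1: where the 10% comes from.**
- Upper limit halved: 0.50 x 19% = 9.5%, rounded to 10%.
- Overall figure halved: 0.50 x 10% = 5%.

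**Step 2: the OR.** (0.30/0.70) / (0.10/0.90) = 3.857, which agrees with the stated value of around 3.85.

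**Step 3: reproduce the stated design.** With control prevalence p0, case exposure is p1 = OR x p0 / (1 - p0 + OR x p0). Let p be the pooled proportion, (54 p1 + 215 p0)/269. Then

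- s0 = sqrt[p(1 - p)(1/54 + 1/215)]
- s1 = sqrt[p1(1 - p1)/54 + p0(1 - p0)/215]
- c = 0.5 x (1/54 + 1/215) = 0.0116 (zero without correction)
- power = Phi[(p1 - p0 - c - 1.96 s0)/s1]

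At p0 = 10%: p1 = 0.2996, p = 0.1401, s0 = 0.0528, s1 = 0.0656. The argument is (0.1996 - 0.0116 - 1.96 x 0.0528)/0.0656 = 1.29, so power is 90.1%. The matching sample size formula at 1:4 gives 54 cases and 270 in total, against the stated 54 and 269. Without correction it gives 48 cases, and one-sided tests need 40 or 46. Of these four forms, only the two-sided corrected one reproduces the plan.

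**Step 4: same method, OR held at 3.85.** At p0 = 5%: p1 = 0.1685, p = 0.0738, s0 = 0.0398, s1 = 0.0531. The argument is (0.1185 - 0.0116 - 1.96 x 0.0398)/0.0531 = 0.54, so power is 70.7%.

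| Control prevalence | Case exposure at OR 3.85 | Power, corrected | Power, uncorrected | OR with 90% power, corrected |
|---|---|---|---|---|
| 10% | 30.0% | 90.1% | 92.8% | 3.84 |
| 9.5% | 28.8% | 89.1% | 92.1% | 3.92 |
| 7.5% | 23.8% | 83.4% | 87.7% | 4.35 |
| 5% | 16.8% | 70.7% | 77.7% | 5.32 |

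At 5%, power is 73.8% for Fisher's exact test and 79.2% for the exact power of the uncorrected Pearson test. The figure depends on the method, but all four stay well below 90%.

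**Step 5: case exposure held at 30% instead.** At p0 = 5% the OR is (0.30/0.70)/(0.05/0.95) = 8.14, and power is 99.0% corrected and 99.4% uncorrected. At 9.5% the OR is 4.08 and corrected power is 91.8%.

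**The case against.** Three objections carry weight.

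*The 5% is never stated.* The opening 10% may be the conclusion announced first, with the 19% and the 50% given next as its justification. Halving it would then apply the duration restriction twice. This reading is possible and would remove the contradiction. Against it, the opening sentence says overall, and the later sentence says long-term. Even on this reading, the planning value is half of an upper limit and no lower value is considered. What stands is that 5% depends on taking the word overall literally.

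*The OR was derived from the prevalence.* The section obtains 3.85 from 30% against 10%, and suggests that case exposure may exceed 30-50%. Power of 71% requires case exposure of only 16.8%. With 30% kept, power rises to about 99%. This is correct, and it rules out a stronger reading that a reader might infer: that 90% is the best case within the document's own range, or that the study is underpowered. Neither is supported. The 90% is the top of the range only with the OR fixed. Still, the section states its minimum detectable effect and its power claim as an OR, so the fixed-OR calculation tests the claim that is made.

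*There is no arithmetical slip in the power.* This too is correct. Given 10%, the OR, sample size and power all reproduce. The fault lies in how the input is derived and labelled. The source of the 19% is not at hand, so the documents do not show how far below it the true value lies.

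**Conclusion.** The point holds in a limited form. The section gives one number to two quantities that, by its own 50% assumption, differ by a factor of two. The long-term 10% is at, or slightly above, half of a stated upper limit, yet it enters the power statement as the expected value.

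For the stated minimum detectable OR of 3.85, power with 54 cases and 215 controls is about 89% at 9.5% control prevalence and falls to about 71% at 5% (about 92% to 78% uncorrected). Equivalently, the OR detectable with 90% power rises from about 3.9 to about 5.3 (corrected).

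This rests on three assumptions: a two-sided 5% test, which the article does not state; the OR held fixed while control prevalence changes; and, for the 5% end only, a literal reading of overall prevalence. The 9.5% end needs no such reading.

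**What to change.** In Power and sample size:

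1. Reconcile overall and long-term prevalence. Say which one the opening 10% is, and name the duration in the power sentence.
2. Label 9.5-10% as the upper limit for long-term use. If the opening 10% does mean overall use, give 5% to 9.5% as the range.
3. Restate power for 54 cases and 215 controls at OR 3.85 over that range as about 71% to 89% (two-sided 5%, continuity-corrected; about 78% to 92% uncorrected), or the OR detectable with 90% power as about 5.3 to 3.9 (corrected). State the alpha, the sidedness and the use of the correction.
4. Say that these figures hold the OR fixed, and that with case exposure held at 30% the OR at 5% is about 8.1 and power about 99%.

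The change is to wording only. No patients need to be added. The cost is a less favourable stated power.
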